#### Secondary and exploratory outcomes

2.8.4

MRI and US findings will be compared using Fisher’s exact test or ordinal logistic regression (adjusted for baseline severity and age). Longitudinal changes in continuous parameters will be analyzed using linear mixed-effects models (LMMs). The SF-12 scores at 12 months will be compared using *t*-tests or the Mann–Whitney *U*-test, with LMMs applied to assess longitudinal profiles. Cytokine levels will be log-transformed if necessary and analyzed using two-way repeated measures ANOVA or LMMs. Correlations between cytokine changes and clinical outcomes will be assessed using Spearman’s rank correlation coefficient. AEs will be tabulated by group and severity (CTCAE grade). The incidence of total AEs, treatment-related AEs, and SAEs will be compared using the Fisher’s exact test.

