#### Cytokine detection

2.4.4

Peripheral blood samples (5 mL) will be collected from all participants at baseline (2 days before the PRP injection) and at 1, 3, 6, and 12 months after the first PRP injection. The blood samples will be centrifuged at 3000 rpm for 15 min to separate the serum, which will be stored at −80 °C for subsequent analysis. The concentrations of pro-inflammatory cytokines (IL-1β, IL-6, IL-8, IL-10, and TNF-*α*) in serum will be measured using enzyme-linked immunosorbent assay (ELISA) with commercially available kits (R&D Systems, USA) in strict accordance with the manufacturer’s instructions. All measurements will be performed in the central laboratory of the Affiliated Hospital of Southwest Medical University to ensure the accuracy and reproducibility of the results.

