#### Longitudinal analysis

2.8.5

For repeated measurements at baseline and at 1, 3, 6, and 12 months, LMMs will be used, including fixed effects for group, time, and the group-by-time interaction, with a random intercept for each participant. An unstructured covariance structure will be specified, and the Kenward–Roger approximation will be used to calculate the denominator degrees of freedom. Age will be included to explore age-by-treatment interactions; if the interaction is significant (*p* < 0.10), stratified analyses will be performed.

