#### Handling of missing data

2.8.7

Missing data will be assumed to be missing at random (MAR). Primary analyses will be conducted using LMMs, which are robust to MAR and utilize all available data. For ANCOVA at 12 months, multiple imputation by chained equations (20 imputations) will be performed using the R package ‘mice,’ including all baseline covariates and outcome values at other time points. Results will be combined using Rubin’s rules. Sensitivity analyses will include complete-case analysis and last observation carried forward (LOCF) imputation.

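### The cytokine analysis leaves open a repeated-measures ANOVA that the plan's own longitudinal rule excludes and that, in its usual form, would discard observed data

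*Protocol article*

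**What the plan says.** Four parts of the protocol article bear on the cytokine analysis.

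- **Section 2.4.4 (Cytokine detection)** and Table 2: blood is drawn "at baseline (2 days before the PRP injection) and at 1, 3, 6, and 12 months after the first PRP injection", so there are five planned measurements per participant.
- **Section 2.8.4 (Secondary and exploratory outcomes):** a general sentence states "Longitudinal changes in continuous parameters will be analyzed using linear mixed-effects models (LMMs"). Two sentences later, cytokines are to be "analyzed using two-way repeated measures ANOVA or LMMs". Nothing says which method applies, or when.
- **Section 2.8.5 (Longitudinal analysis):** "For repeated measurements at baseline and at 1, 3, 6, and 12 months, LMMs will be used". No outcome is exempted. The model has group, time and their interaction as fixed effects, a random intercept per participant, and an unstructured covariance.
- **Section 2.8.7 (Handling of missing data):** the general assumption is "Missing data will be assumed to be missing at random (MAR"). The LMM sentence that follows refers to primary analyses: "Primary analyses will be conducted using LMMs, which are robust to MAR and utilize all available data". Imputation is stated for one analysis only: "For ANCOVA at 12 months, multiple imputation by chained equations (20 imputations) will be performed". Complete-case analysis appears only in a supporting role: "Sensitivity analyses will include complete-case analysis and last observation carried forward (LOCF) imputation".

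**The concern.** The cytokine sentence reopens a choice that two other sentences close, and the two methods treat missing visits differently. Classical repeated-measures ANOVA works on complete rows, as in the usual SPSS procedure (SPSS is one of the two named packages). A participant who misses one of the five samples loses the other four as well. An LMM keeps every observed value.

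Because no imputation is stated for cytokines, taking the ANOVA route would make a complete-case analysis the main cytokine analysis, a role that Section 2.8.7 otherwise gives to sensitivity analyses. Such an analysis is generally valid only under conditions stricter than missing at random (MAR). At stake are the precision of the inflammatory results, which are a named aim of the trial, and an avoidable freedom to choose the method for five cytokines after the data are in.

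**Working it through.** **Plan's own figure.** Section 2.7 gives SD 2.41, difference 1.4, z values 2.24 and 0.84, and 20% dropout.

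- n per group = 2 × (2.24 + 0.84)² × 2.41² / 1.4² = 56.2, rounded up to 57.
- 57 / (1 − 0.20) = 71.25, rounded up to 72 per group, or 144 in total. The stated figures reproduce.

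**Participants kept by a listwise five-visit ANOVA.** With 20% dropout and no other missing sample, 144 × 0.80 = 115.2 remain and 28.8 are lost.

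The protocol gives no rate for isolated missed samples. If a share m of those who complete is assumed to miss each of months 1, 3 and 6 independently, the number kept is 144 × 0.80 × (1 − m)³:

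- m = 2%: 108.4 kept (24.7% lost)
- m = 5%: 98.8 kept (31.4% lost)
- m = 10%: 84.0 kept (41.7% lost)

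**Observed records discarded, from dropout alone.** ANOVA uses 115.2 × 5 = 576 records. The number observed depends on when dropout happens, which the protocol does not state:

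- All before month 1: 144 × (1 + 4 × 0.80) = 604.8 observed; 28.8 discarded (4.8%).
- Spread evenly, 5% before each follow-up visit: 144 × (1 + 0.95 + 0.90 + 0.85 + 0.80) = 648 observed; 72 discarded (11.1%).
- All after month 6: 144 × (4 + 0.80) = 691.2 observed; 115.2 discarded (16.7%).

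**Standard error by visit.** The direct effect at a visit is √(share observed / 0.80). With even dropout:

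| Visit | Share observed | Observed n | ANOVA n | SE ratio |
|---|---|---|---|---|
| Baseline | 1.00 | 144.0 | 115.2 | 1.118 |
| 1 month | 0.95 | 136.8 | 115.2 | 1.090 |
| 3 months | 0.90 | 129.6 | 115.2 | 1.061 |
| 6 months | 0.85 | 122.4 | 115.2 | 1.031 |
| 12 months | 0.80 | 115.2 | 115.2 | 1.000 |

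Across the five visits the average share observed is 648 / 720 = 0.90, which gives a ratio of about 1.06. The ceiling of 1/√0.80 = 1.118 applies at a follow-up visit only if every later dropout attended it. At 12 months the dropouts have no sample under either method, so nothing observed at that visit is lost; the LMM gains there only through correlation with earlier visits.

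**Bias.** An illustrative simulation assumed no true effect, a correlation of 0.6 between visits, 20,000 participants per arm, and roughly 20% dropout after month 6. It compared the complete-case difference at 12 months with an estimate valid under MAR, in SD units:

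- Dropout driven by the month-6 value in the same way in both arms: 0.013 against 0.014.
- Driven by it in one arm only: −0.105 against 0.000.
- Driven by it in opposite directions: −0.225 against −0.016.

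The two estimates agree when the mechanism is common to both arms and separate by about 0.1 to 0.2 SD when it differs. These settings are assumptions, not figures from the protocol.

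**The case against.** The strongest reply is that this is only an unresolved alternative on a secondary outcome in a condensed article. LMM is one of the two permitted methods, and a statistician reading Sections 2.8.4 and 2.8.5 together would probably use it. The final choice could be left to an analysis plan that is not shown. It is true that harm follows only if ANOVA is chosen, run listwise, and applied without prior imputation. However, the article does more than leave a detail open: it names a method that its own general rule does not allow for these visits, so any later plan would have to depart from one statement or the other.

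Four stronger readings are tempting, and the documents do not support them.

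- **That the ANOVA option breaks the plan's missing-data rules.** The MAR assumption is general, but the LMM sentence in Section 2.8.7 names primary analyses. The firm conflict is within Section 2.8.4 and with Section 2.8.5.
- **That standard errors rise by at least 12%.** From dropout alone, 12% is the ceiling. More than that requires isolated missed samples, for which no rate is given.
- **That the cytokine comparison would be biased.** This mainly needs outcome-related dropout that differs between arms, and nothing in the documents points to that in a trial with blinded participants and assessors.
- **That sphericity rules out ANOVA.** Unequal visit spacing does not itself violate sphericity, and standard corrections or the multivariate test deal with violations.

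**Conclusion.** The point holds at low severity. The cytokine sentence permits a method that conflicts with the general longitudinal rule, and there is no criterion for choosing it. The size of the loss rests on the plan's own 144 participants and 20% dropout, on the listwise form of ANOVA, and on no imputation of cytokine data. Under those conditions about 29 participants are removed entirely, and with them between one in twenty and one in six of the cytokine values already collected. The loss of precision is modest and falls mainly on the earlier visits. No primary conclusion, significance level or sample size depends on the choice, and Section 2.7 describes secondary outcomes as not specifically powered and hypothesis-generating.

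**What to change.** In Section 2.8.4, delete the two-way repeated-measures ANOVA alternative from the cytokine sentence and refer to the LMM of Section 2.8.5, taking the group contrast at each visit from that model. Leave log transformation conditional on need, as it is now; nothing here justifies making it mandatory.

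One repair should accompany this. Section 2.8.5 combines a random intercept with an unstructured covariance. If the latter is the residual covariance over the five visits, which is the natural reading with a single random effect, the random intercept is redundant and cannot be separately identified. State one within-patient covariance specification: either the unstructured residual covariance without the random intercept, or the random intercept with a simpler residual structure.

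The cost is a deleted phrase and one clarified sentence. No new data, sample size or method is needed.

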#### Longitudinal analysis

2.8.5

For repeated measurements at baseline and at 1, 3, 6, and 12 months, LMMs will be used, including fixed effects for group, time, and the group-by-time interaction, with a random intercept for each participant. An unstructured covariance structure will be specified, and the Kenward–Roger approximation will be used to calculate the denominator degrees of freedom. Age will be included to explore age-by-treatment interactions; if the interaction is significant (*p* < 0.10), stratified analyses will be performed.

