#### Primary outcome analysis

2.8.3

The primary outcomes (the Chinese version of the CMS and the VAS at 12 months) will be analyzed using analysis of covariance (ANCOVA), with treatment group as a fixed factor and baseline score, age, and time from diagnosis to injection as covariates. A Bonferroni-corrected significance level of *p* < 0.025 (two-tailed) will be applied to each primary outcome to account for multiple comparisons. The study will be considered positive if at least one primary outcome achieves statistical significance at the adjusted 
α
 level, provided that the other outcome shows consistent directional improvement.

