#### Subgroup analyses

2.8.6

Prespecified subgroup analyses for the primary outcomes will be conducted based on age (18–45 years vs. 46–65 years), Ellman classification (Grade I/II vs. Grade III), and time from injury to injection (0–2 weeks vs. 2–4 weeks) to ensure the balance of key confounding factors between the two groups. Interaction tests will be performed within LMMs, and all subgroup analyses will be considered exploratory.

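### The longitudinal mixed model in 2.8.5 takes baseline as a response with a separate mean per arm, so its treatment contrasts are unbiased but less precise than the baseline-adjusted contrast of 2.8.3

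*Protocol article*

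**What the plan says.** Section 2.8.5 (Longitudinal analysis) specifies the model: "For repeated measurements at baseline and at 1, 3, 6, and 12 months, LMMs will be used, including fixed effects for group, time". The same sentence then adds the interaction of these two factors and a participant-level random intercept. It continues: "An unstructured covariance structure will be specified". The only further covariate it names is age, brought in to explore an age-by-treatment interaction. It does not list baseline score as a covariate, does not constrain the arms to a common baseline mean, and does not say which term or visit contrast is the treatment estimate.

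Section 2.8.3 handles the same clinical scores differently. Its 12-month ANCOVA is fitted "with treatment group as a fixed factor and baseline score, age, and time from diagnosis to injection as covariates".

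Mixed models appear in three other places. Section 2.8.4 compares SF-12 at 12 months by an unadjusted two-sample test, "with LMMs applied to assess longitudinal profiles", and offers mixed models as one of two options for cytokines. Section 2.8.6 states: "Interaction tests will be performed within LMMs, and all subgroup analyses will be considered exploratory". Section 2.8.7 says: "Primary analyses will be conducted using LMMs, which are robust to MAR and utilize all available data".

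Section 2.1 places randomisation after baseline assessment.

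**The concern.** Baseline is measured before randomisation, so the two arms share one true baseline mean. The model in 2.8.5 nevertheless estimates a baseline difference freely. A group main effect with a full group-by-time interaction makes the mean model saturated. With complete data, the fit then returns the observed mean of each arm at each visit, whatever covariance matrix is used. Neither the unstructured covariance nor the random intercept therefore supplies a baseline adjustment.

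Two treatment contrasts remain: the raw difference at a visit, and the interaction term, which is the difference in change from baseline. A chance baseline imbalance is carried into the first in proportion to the correlation and over-corrected by the second. Precision is at stake in every longitudinal treatment estimate. So is consistency, because the mixed model and the ANCOVA can give different answers for the same score at 12 months for no substantive reason.

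**Working it through.** **Inputs from the protocol (2.7).** VAS difference 1.4 cm, SD 2.41 cm, two-sided alpha 0.025, power 80%, 57 evaluable per group, 20% dropout, 72 per group randomised.

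**Assumed.** The correlation rho between baseline and the visit is not in the documents; 0.3, 0.5 and 0.7 are used. Variances are taken as equal at baseline and at the visit.

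**The plan's own figure.** n = 2 × 3.08² × 2.41² / 1.4² = 56.2, so 57 per group; 57 / 0.8 = 71.25, so 72 per group and 144 in total. This reproduces. The calculation compares two independent means with no baseline adjustment.

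**Variances per contrast, in units of 2 × SD² / n.**
- Raw difference at the visit: 1
- Difference in change: 2(1 − rho)
- Baseline-adjusted (ANCOVA or common-baseline mixed model): 1 − rho²

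**Ratios to the adjusted contrast, complete data.** Raw: 1 / (1 − rho²). Change: 2(1 − rho) / (1 − rho²) = 2 / (1 + rho).

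| rho | Raw | Change |
|---|---|---|
| 0.3 | 1 / 0.91 = 1.10 | 2 / 1.3 = 1.54 |
| 0.5 | 1 / 0.75 = 1.33 | 2 / 1.5 = 1.33 |
| 0.7 | 1 / 0.51 = 1.96 | 2 / 1.7 = 1.18 |

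An exact generalised least squares calculation for the five-visit model gives the same ratios. A simulation of 20,000 trials with 57 per arm, in which the ANCOVA slope is estimated, gives 1.09, 1.33 and 1.94 (raw) and 1.53, 1.32 and 1.15 (change).

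**Better of the two contrasts.** They cross where 1 / (1 − rho²) = 2 / (1 + rho), that is at rho = 0.5, with ratio 1.33. This is the largest loss if the better contrast were always chosen.

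**With dropout.** Take 72 per arm, 20% monotone dropout spread evenly after months 1, 3 and 6, and equal correlation between visits. At rho 0.3, 0.5 and 0.7 the excess variance at 12 months is 8, 28 and 81% (raw) and 44, 28 and 15% (change).

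**If correlation decays with each successive visit.** With correlation r between adjacent visits, baseline to 12 months is r⁴. For r = 0.3, 0.5 and 0.7, the raw ratio at 12 months is 1.00, 1.00 and 1.06, and the change ratio is 1.98, 1.88 and 1.61. At 1 month the correlation is r itself, and the table above applies.

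**Power with the trial's inputs.** The standardised difference for the raw contrast is 1.4 / (2.41 × √(2/57)) = 3.10, and the critical value is 2.24. Dividing 3.10 by the square root of each variance above, subtracting 2.24 and reading off the normal distribution gives:

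| rho | Raw | Change | Baseline-adjusted |
|---|---|---|---|
| 0.3 | 80.5% | 64.8% | 84.4% |
| 0.5 | 80.5% | 80.5% | 91.0% |
| 0.7 | 80.5% | 96.1% | 98.2% |

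**The case against.** The strongest reply is that the model is conventional and valid. Both contrasts are unbiased under randomisation, and the model contradicts nothing. That stands: the point is about efficiency. It is still fair to raise, because 2.8.5 already fixes the visits, fixed effects, covariance and degrees-of-freedom method. The point concerns a model that is stated, not a detail left to a later document.

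Second, the main result is protected, since 2.8.3 adjusts for baseline score. Section 2.7 also calls the secondary outcomes hypothesis-generating and not specifically powered. Both are true and limit the importance. A reader might infer from the sentence in 2.8.7 that the inefficient model governs the primary outcomes. The documents do not settle that: 2.8.3 names ANCOVA, and 2.8.7 itself provides imputation for the 12-month ANCOVA. Which method is primary is a separate question, and this point does not rest on it.

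Third, a reader might infer a general inflation of 10 to 100%. That would pool two different contrasts over an assumed correlation. If rho to a visit is near zero, the raw contrast loses almost nothing while the change contrast has nearly double the variance. Nor does the trial become underpowered as such: 2.7 sized it on unadjusted means, so the raw contrast keeps the planned power, and the change contrast falls below it only when rho is under 0.5.

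Fourth, 2.8.2 adds baseline variables with p < 0.10 as covariates in adjusted analyses. That rule is conditional on a test result, and it does not recover the precision that routine adjustment gives.

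**Conclusion.** The point holds as a loss of precision in the mixed-model estimates: SF-12 profiles, cytokines where mixed models are used, and CMS and VAS over time, including the exploratory subgroup tests fitted in the same model. For SF-12, no analysis stated in 2.8.4 adjusts for baseline score.

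The size depends on rho, which the documents do not give, and on which contrast is reported, which 2.8.5 does not say. Over rho of 0.3 to 0.7 the excess is substantial for at least one of the two contrasts, and planned dropout reduces it without removing it. The figures assume equal variances over time and, for the dropout case, monotone loss with equal correlations.

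There is no bias, and the 12-month ANCOVA in 2.8.3 is untouched. This is a worthwhile improvement to the secondary and longitudinal analyses, not a threat to the trial's main conclusion.

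**What to change.** Amend 2.8.5 in one of two ways.

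1. Keep baseline among the responses but give both arms a common baseline mean: time effects, plus group-by-time terms for 1, 3, 6 and 12 months only. Keep the unstructured covariance, because in this model it carries the baseline adjustment.
2. Remove baseline from the responses and enter baseline score as a covariate with a baseline-by-time term.

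In either case, report the group contrast at each visit and name 12 months as the main one.

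The cost is about one sentence, and the data are already scheduled in Table 2. One assumption deserves a line. The common mean follows from randomisation, whereas 2.8 analyses only randomised participants who receive at least one injection. Patients and the injecting physician are blinded, so differential loss before the first injection is unlikely, but the number excluded in each arm should be reported.

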#### Subgroup analyses

2.8.6

Prespecified subgroup analyses for the primary outcomes will be conducted based on age (18–45 years vs. 46–65 years), Ellman classification (Grade I/II vs. Grade III), and time from injury to injection (0–2 weeks vs. 2–4 weeks) to ensure the balance of key confounding factors between the two groups. Interaction tests will be performed within LMMs, and all subgroup analyses will be considered exploratory.

#### Handling of missing data

2.8.7

Missing data will be assumed to be missing at random (MAR). Primary analyses will be conducted using LMMs, which are robust to MAR and utilize all available data. For ANCOVA at 12 months, multiple imputation by chained equations (20 imputations) will be performed using the R package ‘mice,’ including all baseline covariates and outcome values at other time points. Results will be combined using Rubin’s rules. Sensitivity analyses will include complete-case analysis and last observation carried forward (LOCF) imputation.

#### Safety analysis

2.8.8

Safety will be assessed for all participants receiving at least one PRP injection. AEs will be coded using MedDRAs and summarized by SOC and Preferred Term (PT). Descriptive statistics and 95% confidence intervals will be reported; no formal hypothesis testing is planned for safety endpoints.

## Discussion

3

Tendons are bundles of parallel fibrous structures that lack blood supply, making them difficult to heal if damaged. After a tendon laceration or rupture, the tissue is often repaired by scar formation, which cannot restore the tendon’s normal mechanical structure. PRP, an emerging biological treatment, has been widely applied to the management of tendinopathy. However, heterogeneity in PRP preparation and variability in its cellular composition fuels ongoing controversy over its clinical efficacy. This study has been designed to investigate the role of leukocytes and PLTs in PRP for tendinopathy. By comparing two distinct PRP formulations, this study will provide critical evidence to guide the application of optimal PRP composition for tendinopathy.

It is imperative to consider the 5R’s of prescribing: “right patient, right drug, right dose, right route, and right time.”

Patient characteristics may be the factor directly affecting the quantity of PRP. When evaluating the quality of PRP, it is necessary to consider patient-related variables that could affect its composition, such as female sex, age over 50 years, traumatic clinical conditions, or a history of medications such as clopidogrel and dabigatran (40). The biological status of the tendon determines the clinical effects of PRP (15). Conservative treatment can be the first option after evaluating related risk factors that may lead to failure of non-operative management (29, 41). When non-operative management fails, surgical treatment remains the optimal approach for RCI with significant symptoms, especially articular-side tears exceeding 6 mm of the rotator cuff footprint or complete tears (29, 42). Therefore, choosing the “right patient” is essential in clinical practice.

A standardized preparation procedure is an important factor influencing clinical efficacy, as it has a direct impact on the final composition and quality of PRP. PRP can be formulated in multiple ways, and there is currently no internationally accepted consensus to standardize its formulation. It seems that the concentration of PRP components produced by the machine is relatively stable. In fact, the concentrations of PLTs, leukocytes, and GFs may vary depending on the equipment used. Several factors can affect the quality of PRP products, including anticoagulant type, g-force, centrifugation duration, cell volume, and separation accuracy (40). To achieve optimal clinical effects, PRP components and doses should be tailored to the specific scenario. In this study, the PLT concentration for Group 1 is set at 2.5–3.5-fold enrichment (1.74 ± 0.20 × 10^9^/2 mL) and for Group 2 at 4.0–6.0-fold enrichment (2.66 ± 0.52 × 10^9^/2 mL), administered once per week for two consecutive weeks. Compared to higher concentrations with doses of 4–6 mL used in knee osteoarthritis, the PRP dose for tendinopathy is usually set at 2–3 mL, as the injection strategy focuses on the injured or degenerated tendons rather than the intra-articular space. This dosage scheme is based on the anatomical characteristics of the shoulder joint and clinical practice of PRP for RCI. It has been reported that a 3–5-fold enrichment of PLTs is recommended as the optimal concentration for tendinopathy (43). Higher concentrations of PRP may lead to tendon overgrowth and even cause shoulder impingement syndrome (44). Excessively high PRP concentrations may even have an inhibitory effect on cell proliferation, migration, and the production of type I collagen (45). As an important part of tissue healing, inflammatory cells such as neutrophils and monocytes migrate to the injured area and remove necrotic tissue through phagocytosis (15). The leukocyte concentration plays a crucial role in PRP function, influencing both anabolic and catabolic processes, which are often time-dependent (46). LR-PRP can induce a pronounced inflammatory response, increasing cytokine levels such as IL-6, IL-10, and TNF-α, especially TNF-α, which inhibits apoptotic cell death by activating the NF-kB signaling pathway. Therefore, LR-PRP seems to have a more effective regeneration tendency in tendon healing at the early stage (43). In contrast, LP-PRP can improve the biomechanical properties of tendons, including tensile stress and stiffness, due to its beneficial effects on tendon proliferation, collagen synthesis, and inflammation modulation (15, 47). However, in the application of LP-PRP, this approach may be more suitable for chronic tendinopathy (48). PRP-related approaches should be further refined in terms of preparation parameters to achieve the “right drug,” tailored to specific clinical indications and usage.

The unstandardized timing of PRP injections also hinders the evaluation of efficacy across different studies. Although previous studies have investigated different types of PRP in acute or chronic tendon injury phases, the optimal intervention time points remain uncertain (3, 15, 40, 46). The specific PRP formulation should align with the tissue healing time point (49). For example, the natural healing process can be delayed or interrupted by PRP injections during the acute inflammatory phase, as the dual pro-and anti-inflammatory properties of PRP may perturb the orderly inflammatory response (49).

The objective of PRP injection is to minimize pain and reduce the risk of tendon tears. The specific site of the PRP injection is a key factor influencing its efficacy. Pain-generating areas are defined as areas with a high density of nociceptive receptors, including the subacromial bursa, coracoacromial ligament, and the long head of the biceps tendon. These areas are innervated by the same nerves—the suprascapular, lateral pectoral, and axillary nerves—that also innervate the injured rotator cuff. Shoulder pain originating from RCI can be transmitted to distinct pain generator zones via three neural bridges (50). Consequently, when designing injection strategies and performing selective nerve blocks, clinicians should target not only the injured tendon but also the pain generator areas and their parent nerve trunks to discrepancies in efficacy. The injection procedure can ensure precise delivery of PRP to the injured site under US guidance.

Most previous studies investigated the role of leukocytes or PLTs in clinical practice. Based on current research, this study will first investigate the synergistic effects of PRP components and their concentrations, and will subsequently analyze the relationships between these factors and patient variables in a stepwise manner. This protocol reports a detailed preparation method and PRP characteristics, aiming to stimulate discussion on the optimal PRP formulations for different musculoskeletal conditions and to promote the development of standardized PRP guidelines in the future. Although this study focuses on several factors affecting the practical efficacy of PRP, many uncertainties may still exist in its clinical application, which need to be reported and investigated in further studies. Future studies should expand the sample size, extend the follow-up period, and include multi-center data to validate the results. In addition, further *in vitro* experiments are needed to explore the specific mechanism underlying the synergistic effects of PLT and leukocyte concentrations on rotator cuff tendon healing.

